**Methods:**

A randomized, double-blind (surgeon-, anesthesiologist-, patient-, data-monitor-blinded), placebo-controlled trial of tranexamic acid during cystectomy was initiated in June 2013. Prior to incision, the intervention arm participants receive a 10 mg/kg loading dose of intravenously administered tranexamic acid, followed by a 5 mg/kg/h maintenance infusion. In the control arm, the patient receives an identical volume of normal saline that is indistinguishable from the intervention. The primary outcome is any blood transfusion from the start of surgery up to 30 days post operative. There are no strict criteria to mandate the transfusion of blood products. The decision to transfuse is entirely at the discretion of the treating physicians who are blinded to patient allocation. Physicians are allowed to utilize all resources to make transfusion decisions, including serum hemoglobin concentration and vital signs. To date, 147 patients of a planned 354 have been randomized to the study.

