#### Blinding of intervention

Tranexamic acid, diluted in saline or undiluted, is clear, colorless, and indistinguishable from saline both at rest and when vigorously agitated [16]. Matching placebo maintenance infusions are identical saline bags without discarded saline or added drug in order to maintain the same volume and weight. To minimize sources of selection and ascertainment biases, anesthesiologists, surgeons, investigators, research staff, and members of the Data Safety and Monitoring Board (DSMB) are all blinded to randomization schemes and treatments administered; only the statistician has access to randomization schemes. The research pharmacist does not have contact with the study team or the patient, and is expressly forbidden to discuss individual treatment allocation with the operating room and clinical care team (a signed confidentiality agreement is obtained from each site research pharmacy personnel). Clinical teams are permitted to unmask treatment allocation only under exceptional circumstances. A request to unmask allocation for an individual patient is made to the coordinating center. A clinical member of the Executive Committee (24 h availability) reviews the request to ensure that it is necessary, based on pre-established criteria.

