### Statistical methods

Patient baseline characteristics will be summarized with descriptive statistics. Comparative analyses will be based on an intention-to-treat principle (i.e., based on the participant’s randomized study arm allocation). To address the primary objective of the effect of systemic tranexamic acid compared to placebo on the proportion of patients requiring red blood cell transfusion within 30 days, a chi-square test of proportions will be used. The effect size will be derived with an unadjusted RR and 95% confidence limits. If notable baseline imbalances are present, an adjusted estimate will be derived for the RR by stratifying on the potential confounders and pooling with a Mantel-Haenszel RR estimator. Secondary analyses of the effect of tranexamic acid on the volume of intraoperative blood loss and the perioperative adverse event rate will follow in a similar fashion, using chi-square or *t* tests, depending the outcome, and logistic or linear regression to estimate the magnitude of effect. A Poisson regression model will be fit to assess the difference in the number of transfused blood products between trial arms. Subgroup analyses will also be presented for clinically important baseline factors that may influence the effect of the drug, including sex, patient age (< 60 years, 60–70 years, 71–80 years, and < 80 years), preoperative hemoglobin (< 100 g/L, 100–120 g/L, and > 120 g/L), and previous history of cardiac disease (yes/no). Data is compiled by the study statistician and reviewed by an independent DSMB every 6 months. No interim analysis is planned for this trial.

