### Data monitoring

#### Steering Committee and Data Safety Monitoring Board

All collaborators, site investigators, and research staff serve on the Trial Steering Committee. The committee aims to meet via teleconference every 6 months.

The DSMB has full responsibility for the monitoring of response variables for adverse events throughout the trial. This committee functions independently from all other study committees and serves in an advisory role to the Executive Committee. The DSMB consists of three individuals, covering requisite expertise in clinical epidemiology, biostatistics, urologic oncology, and anesthesia, and may consult external experts regarding specific outcome evaluations.

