#### Stopping rules

No early stopping rules have been developed for this trial; early stopping criteria are at the discretion of the members of the independent DSMB. The DSMB may make recommendations to terminate or continue the study. Early stopping of the study will only be based on appraisal of SAEs and will be at the discretion of the clinical experts of the independent DSMB.

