## Discussion

Blood loss resulting in transfusion is common during radical cystectomy. As shown in previous studies, tranexamic acid has the potential to significantly reduce operative blood loss. However, based on a recent survey of urologists and a recent systematic review of the academic literature, tranexamic acid is not commonly used by urologists and no previous trials have assessed the benefits and harms of this drug for patients treated with radical cystectomy. To the best of our knowledge, this is the only registered trial evaluating a lysine analog during cystectomy (ClinicalTrials.gov search on 7 July 2017).

Use of tranexamic acid during surgery at the study dose is inexpensive (less than 40 Canadian dollars per surgical case), technically easy to administer, and has been successfully performed in several trials evaluating other surgical procedures. Anesthesiologists are familiar with the use of tranexamic acid during cardiac surgery, orthopedic surgery, and other procedures where significant blood loss is anticipated. However, the uncritical use of tranexamic acid is not warranted without rigorous and definitive evidence to inform clinical practice. While most individual studies of tranexamic acid for non-urological surgeries revealed benefit of the drug, some did not. For example, in a study of myomectomy (surgical removal of benign tumors from the uterus), 50 patients were randomized to tranexamic acid and 50 were randomized to a control group which did not receive tranexamic acid [24]. In this study, tranexamic acid did not reduce the risk of receiving an allogeneic blood transfusion (RR 1.50, 95% CI 0.75 to 3.01). This evidence conflicts with findings that tranexamic acid was efficacious in reducing the number of transfusions required in other pelvic surgeries (e.g., radical prostatectomy) [22] and further highlights the need for more in-depth investigation of the effectiveness of tranexamic acid in pelvic surgery through a RCT. Furthermore, cystectomy patients are at high risk of thromboembolic complications and, theoretically, lysine analogs may increase this risk.

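### The DSMB is blinded to treatment although SAE appraisal is the only basis for early stopping, and no route to by-arm safety data or to arm identity is stated

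*Protocol article*

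**What the plan says.** All references are to the protocol article.

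- **Blinding of intervention:** "members of the Data Safety and Monitoring Board (DSMB) are all blinded to randomization schemes and treatments administered". The stated purpose is to limit selection and ascertainment bias. On who holds the allocation, the section says "only the statistician has access to randomization schemes" (Blinding of allocation arm adds that pharmacy research staff hold their own site's schedule). The only unmasking described is for an individual patient, requested by a clinical team and reviewed by a clinical member of the Executive Committee.
- **Steering Committee and Data Safety Monitoring Board:** "The DSMB has full responsibility for the monitoring of response variables for adverse events throughout the trial". The board is independent of the other committees and advisory.
- **Stopping rules:** "No early stopping rules have been developed for this trial", and "Early stopping of the study will only be based on appraisal of SAEs", at the discretion of the board's clinical experts.
- **Statistical methods:** "Data is compiled by the study statistician and reviewed by an independent DSMB every 6 months". No interim analysis is planned; Harms repeats this.
- **Discussion:** "cystectomy patients are at high risk of thromboembolic complications and, theoretically, lysine analogs may increase this risk". The risk summary before Auditing likewise names vascular occlusive events, with seizures, as events under watch.
- **Abstract, Methods:** the trial is described as "double-blind (surgeon-, anesthesiologist-, patient-, data-monitor-blinded").

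**The concern.** The board that alone advises on stopping for safety is, by an explicit rule, kept from knowing who received what. DVT, PE, MI and stroke are complications that these patients can be expected to have anyway. A single such event under blinding says little about the drug, so an excess caused by tranexamic acid shows only when the arms are compared. Nothing in the article assures the DSMB of that comparison, and nothing tells it how to find out which arm is which.

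This goes beyond missing detail, because the blinding of the DSMB is stated outright and pulls against the remit the article gives that board. The reason given for the blinding also fits the DSMB poorly: nothing in the article has its members enrolling patients, giving care or ascertaining outcomes.

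At stake is participant safety during the remaining enrolment. 147 of 354 patients had been randomized and five of 13 sites were not yet active, so 354 − 147 = 207 patients were still to be enrolled.

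**Working it through.** The plan gives no figure on this point to reproduce. The check sets the statements side by side and then illustrates the size.

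**1. What each form of report would tell the board**

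| Report to DSMB | Allowed by the blinding rule as written? | Shows an imbalance? | Shows which arm is the drug? |
|---|---|---|---|
| Single cases or pooled totals | Yes | No | No |
| Tables by masked arm A/B | Yes; reveals neither the scheme nor the treatment | Yes | No |
| Tables by coded arm, codes on request | Tables yes, code access no | Yes | Yes, if requested |

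The article does not say which of the first two rows applies. It contains no provision for the third. The statistician who compiles the DSMB data has the scheme, so all three are feasible.

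**2. Illustration**

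Inputs: 177 per arm and 354 in total (Sample size); 147 randomized so far (Trial status); 1:1 allocation (Randomization). The thrombotic risks are assumptions, since the protocol gives none.

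Take 5% on placebo and 10% on drug:
- Expected events: 177 × 0.05 = 8.9 and 177 × 0.10 = 17.7, about 9 versus 18.
- Pooled rate: (5% + 10%) / 2 = 7.5%, that is 354 × 0.075 = 26.6 events at full enrolment, or 147 × 0.075 = 11.0 at the reported accrual.
- A risk of 7.5% in both arms has the same pooled expectation, so the pooled figure carries no between-arm information.

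**3. What by-arm data would add**

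The probability of a two-sided Fisher p<0.05 in the direction of harm was obtained by summing the product of the two binomial probabilities over all qualifying tables, with 177 per arm:

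| Assumed placebo risk | Ratio | Expected events, placebo vs drug | Pooled rate | Probability |
|---|---|---|---|---|
| 3% | 2 | 5.3 vs 10.6 | 4.5% | 0.19 |
| 3% | 3 | 5.3 vs 15.9 | 6.0% | 0.60 |
| 5% | 2 | 8.9 vs 17.7 | 7.5% | 0.35 |
| 5% | 3 | 8.9 vs 26.6 | 10.0% | 0.86 |
| 8% | 2 | 14.2 vs 28.3 | 12.0% | 0.59 |
| 8% | 3 | 14.2 vs 42.5 | 16.0% | 0.98 |

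At 147 patients, the 5% versus 10% case gives about 0.13 to 0.18, depending on which arm holds the odd patient.

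By-arm tables are therefore a weak detector of a doubling and a good one of a tripling when the background risk is 5% or more. The p<0.05 mark is only a yardstick here; a board may act on less.

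**The case against.** **The stronger reading does not hold.** A reader might infer that the DSMB cannot see a thrombotic imbalance at all. The article does not support that. Nowhere does it say that the reports are pooled, and masked A/B tables are compatible with the blinding rule. A reader might also infer that the DSMB is the only safety safeguard. It is not: patients with thromboembolic disease that is active or diagnosed within a year are excluded, severe adverse events go to the coordinating center, adverse events go to Health Canada, and individual unmasking requests are reviewed around the clock. None of these compares the arms, but they exist.

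**Report format may sit elsewhere.** An article commonly leaves the layout of DSMB reports and access to codes to a charter or the full protocol. That stands as to layout. It does not dispose of the point, because the article states the blinding of the DSMB to treatment as a rule. If a charter gives the board access to codes, that statement is inaccurate and should be corrected.

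**The size is assumed, and the cited evidence leans the other way.** The risk summary reports RR 0.71 for DVT, 0.67 for PE and 0.84 for vascular occlusive events in the trauma trial; stroke is the exception at 1.23 (95% CI 0.49 to 3.07). By-arm reports would often miss a doubling in any case, and a pooled rate above expectation could itself prompt the board to ask for more. All of this is fair and limits the priority. It does not help a board that sees an A/B imbalance and has no stated way to learn its direction, since an excess on drug and an excess on placebo bear on stopping in opposite ways.

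**The abstract's term is ambiguous.** The data monitor there may be the study monitor described under Monitoring procedures, not the DSMB.

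**Conclusion.** The concern holds in a limited form. The article blinds the DSMB to treatment, makes the board's appraisal of SAEs the only basis for early stopping, and provides neither by-arm reports nor a route to arm identity. Sight of a between-arm thrombotic excess is therefore not assured, and attribution to the drug is not possible under the rules as written, even from A/B tables.

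This conclusion rests on the text alone. The numerical illustration rests on assumed placebo risks of 3% to 8%. Over that range, by-arm data at full enrolment would reach p<0.05 with probability 0.19 to 0.59 for a doubling and 0.60 to 0.98 for a tripling, while pooled data cannot separate either from a higher background rate. The sample size and the primary analysis are unaffected.

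Priority: should-fix, as a cheap improvement to participant safety. It is not a must-fix, since masked by-arm reporting may already take place and other safeguards exist.

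**What to change.** Reconcile Blinding of intervention with Statistical methods, the DSMB section and Stopping rules by stating that:

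1. the study statistician gives the DSMB a closed safety report every 6 months, by coded arm, covering SAEs, DVT, PE, MI, cerebral infarction, seizures and deaths;
2. the DSMB may obtain the arm codes on request;
3. everyone else who is now blinded stays blinded;
4. the report contains no efficacy comparison.

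Amend the abstract's description of the data monitor as blinded only if it refers to the DSMB. If a charter already contains these provisions, it is enough to correct the blinding statement and refer to the charter.

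Cost: a short protocol amendment or charter wording. The statistician already holds the allocation and compiles the data, so no new role is needed. With no efficacy look, no alpha is spent and the sample size does not change. The one downside is that an independent, advisory board would be less fully masked.

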### Trial management

The Ottawa Methods Center of the Ottawa Hospital Research Institute is responsible for coordination and day-to-day management of the trial, where the investigators have extensive experience of conducting multi-center trials. The data management services group is responsible for initial database design and setup, web-based online enrollment, and randomization, electronic data-form maintenance, and data storage. About 20% of documents at each site are reviewed for data quality. Each site has a site investigator and at least one research coordinator dedicated to this project. The site research coordinator has the responsibility to verify patient eligibility, seek informed consent, attend procedures and randomize patients via the online website, accurately fill out all data collection forms, and report any serious adverse events (SAEs).

### Statistical methods

Patient baseline characteristics will be summarized with descriptive statistics. Comparative analyses will be based on an intention-to-treat principle (i.e., based on the participant’s randomized study arm allocation). To address the primary objective of the effect of systemic tranexamic acid compared to placebo on the proportion of patients requiring red blood cell transfusion within 30 days, a chi-square test of proportions will be used. The effect size will be derived with an unadjusted RR and 95% confidence limits. If notable baseline imbalances are present, an adjusted estimate will be derived for the RR by stratifying on the potential confounders and pooling with a Mantel-Haenszel RR estimator. Secondary analyses of the effect of tranexamic acid on the volume of intraoperative blood loss and the perioperative adverse event rate will follow in a similar fashion, using chi-square or *t* tests, depending the outcome, and logistic or linear regression to estimate the magnitude of effect. A Poisson regression model will be fit to assess the difference in the number of transfused blood products between trial arms. Subgroup analyses will also be presented for clinically important baseline factors that may influence the effect of the drug, including sex, patient age (< 60 years, 60–70 years, 71–80 years, and < 80 years), preoperative hemoglobin (< 100 g/L, 100–120 g/L, and > 120 g/L), and previous history of cardiac disease (yes/no). Data is compiled by the study statistician and reviewed by an independent DSMB every 6 months. No interim analysis is planned for this trial.

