## Background

Bladder cancer is the sixth most common cancer in North America with an estimated 80,000 new diagnoses in 2011 [1, 2]. Among incident cancers it is estimated that 8% (6400 per year) will undergo radical cystectomy [3]. Radical cystectomy is an advanced surgical procedure that involves removal of the urinary bladder, adjacent organs, and pelvic lymph nodes. Removal of the urinary bladder also necessitates urinary reconstruction using an isolated segment of small or large intestine for urinary diversion. The extensive extirpative and reconstructive components of this surgery result in prolonged operative times and are associated with significant risk of complications including high risk of perioperative bleeding and subsequent need for blood transfusion [4]. Among individual surgeons at institutions that perform many procedures, median intraoperative blood loss is between 600 and 1700 mL [5–7]. The incidence of at least one intraoperative blood transfusion is 9 to 67% [5–9], and the postoperative transfusion risk is at least 15% [6, 9]. Among cystectomy patients who receive transfusion, a median of 2 units of blood cells are given [6, 9].

Lysine analog drugs are synthetic derivatives of the amino acid lysine that reversibly block lysine-binding sites on plasminogen molecules [10]. This action prevents the conversion of plasminogen to plasmin, the active enzyme that degrades fibrin clots. Therefore, lysine analogs decrease the breakdown of clots and are considered anti-fibrinolytics. There are two commonly studied lysine analogs, tranexamic acid and epsilon-aminocaproic acid. Both of these drugs have been shown to decrease blood transfusion need during some surgeries without a significant increase in adverse events.

In 2011, urologists who specialize in cancer treatment (members of the Society of Urologic Oncology) were surveyed about the methods they used to prevent blood loss during radical cystectomy [11]. Respondents were asked about their use of systematic techniques, systemic drugs, and topical agents to reduce blood loss and prevent blood transfusion. Topical agents were commonly used among expert urologists (73% used oxidized cellulose polymer; 53% used gelatin and thrombin matrix) and 28% used at least one systematic technique such as autologous blood recovery. Systemic drugs, such as lysine analogs, were used by only 5% of surgeons.

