### Study outcomes

#### Primary outcome

The primary outcome of the trial is whether or not the patient was transfused at least 1 unit of packed red blood cells up to 30 days post operative. We will compare the proportion transfused at least 1 unit of packed red blood cells between tranexamic acid and placebo study arms. In keeping with our pragmatic approach and difficulty in defining a transfusion protocol, there are no strict criteria to mandate the transfusion of blood products. The decision to transfuse is entirely at the discretion of the treating physicians who are blinded to patient allocation. Physicians are allowed to utilize all resources to make transfusion decisions, including serum hemoglobin concentration and vital signs.

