### Allocation of intervention

#### Randomization

Eligible and consenting patients are randomized using computer-generated random numbers before surgery in a 1:1 allocation ratio to one of the two arms of the study using permuted blocks of variable length (2, 4, and 6). Patients are also stratified by center.

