## Trial status

Since the trial opened in June 2013, 147 patients have been accrued and successfully randomized. 13 research sites are participating in the trial, eight of which are currently active. The remaining five sites are in the process of submitting their regulatory documents before site setup can begin. To date, no SAEs have been reported that were considered related to the study drug.

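### Randomization is stratified by center but the primary test and RR ignore center: if centers differ in transfusion rate, the analysis is valid but somewhat conservative, and a center-stratified analysis would recover a little power at no cost

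*Protocol article*

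**What the plan says.** Under Randomization, allocation is 1:1 "using permuted blocks of variable length (2, 4, and 6"), and "Patients are also stratified by center". Trial status reports that "13 research sites are participating in the trial", of which eight are active.

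Under Statistical methods, the primary comparison and its estimate are both fixed: "a chi-square test of proportions will be used. The effect size will be derived with an unadjusted RR and 95% confidence limits". The only route to an adjusted RR is conditional. If baseline factors turn out notably imbalanced, the RR is to be stratified on possible confounders and pooled by Mantel-Haenszel. That clause concerns the estimate and leaves the primary test as it is. Nothing else in the article brings center into the primary analysis.

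Two statements bear on whether centers might differ. Under Primary outcome there are no strict transfusion criteria, and "The decision to transfuse is entirely at the discretion of the treating physicians who are blinded to patient allocation". The Background reports, from published series, that "The incidence of at least one intraoperative blood transfusion is 9 to 67" percent.

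**The concern.** Permuted blocks within center force near-equal arms at each site. Differences between sites therefore largely cancel out of the treatment comparison. The pooled chi-square test and the usual interval for an unadjusted RR still count those differences as noise. If center predicts transfusion, the standard error is too large, the test rejects less often than 5% under the null, and some of the precision bought by the stratified randomization is not used.

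The imbalance clause does not remedy this. Blocking keeps center balanced, so center would hardly ever qualify as imbalanced. The reason to include it is also not confounding but matching the variance to the design. The word unadjusted is written into the article, so this is a stated choice and not a detail left to an analysis plan.

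**Working it through.** **Inputs from the article.** 50% transfused on placebo and 35% on tranexamic acid (RR 0.70), two-sided alpha 5%, power 80%, 340 patients raised to 354 (Sample size); 13 sites (Trial status); blocks of 2, 4 and 6 within center (Randomization). **Assumed:** the standard deviation (SD) τ of the true placebo transfusion rate between centers, which the article does not give.

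**The plan's own figure.** With the mean rate 0.425,

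n per arm = [1.960·√(2·0.425·0.575) + 0.8416·√(0.50·0.50 + 0.35·0.65)]² / 0.15² = (1.3702 + 0.5816)² / 0.0225 = 169.3, so 170 per arm and 340 in total.

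340 / 0.98² = 354.0, which gives the stated 354. The sample size reproduces, and it rests on an unadjusted comparison.

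**Large-sample type I error.** Under the null with a mean rate of 0.5, the pooled variance per patient is 0.25. With balance within centers, the variance that actually drives the difference is 0.25 − τ². The chi-square test therefore has true size 2·[1 − Φ(1.960 / √(1 − τ²/0.25))]:

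- τ = 0: 5.0%
- τ = 0.10: 1.960/√0.96 = 2.000, size 4.5%
- τ = 0.15: 1.960/√0.91 = 2.055, size 4.0%
- τ = 0.20: 1.960/√0.84 = 2.138, size 3.2%

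**Large-sample power.** Take 177 per arm and a constant RR of 0.70 in every center. The true standard error is SE = √[(0.25 − τ² + 0.2275 − 0.49τ²)/177]. Chi-square uses the null standard error √[2·0.425·0.575/177]. The stratified test uses about √[2·(0.425·0.575 − 0.85²τ²)/177]. Power is Φ[(0.15 − 1.960·null SE)/SE]:

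- τ = 0: 81.7% for both
- τ = 0.10: 82.1% against 82.9%, loss 0.8 points
- τ = 0.15: 82.6% against 84.3%, loss 1.7 points
- τ = 0.20: 83.3% against 86.4%, loss 3.0 points

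**Simulation.** This used 13 unequal centers, 354 patients, the stated blocks within center, and 5,000 to 8,000 replicates per cell, repeated with different random draws and center sizes. Each pair is pooled chi-square / center-stratified Cochran-Mantel-Haenszel (CMH). Ranges are over the repeats.

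| Assumed center SD | Type I error, % | Power, % | Power loss, points |
|---|---|---|---|
| 0 | 4.9 / 4.9 | 81.4 to 81.8 / 81.5 to 81.8 | 0 to 0.1 |
| 10 points | 4.3 to 4.7 / 5.0 to 5.2 | 81.6 to 83.4 / 82.3 to 83.9 | 0.5 to 0.8 |
| 15 points | 3.8 to 4.5 / 4.5 to 5.3 | 81.3 to 82.0 / 82.9 to 83.5 | 1.5 to 1.7 |
| 20 points | 3.3 to 3.7 / 4.9 to 5.2 | 81.4 to 82.3 / 84.5 to 85.1 | 2.8 to 3.1 |

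Monte Carlo error on one power figure is about 0.4 to 0.5 points (√(0.82·0.18/8000) = 0.43), so the third digit should not be read closely.

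**Interval width.** In one of these runs the mean standard error of log RR, unadjusted against stratified, was 0.128 against 0.125 at SD 15 (ratio 1.02) and 0.129 against 0.1225 at SD 20 (ratio 1.05). The unadjusted interval is thus about 2% and 5% wider on the log scale.

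**A different model.** Normal center effects on the logit scale were run with equal-sized centers and overall rates held at 50% and 35%. With 5th to 95th percentiles of placebo rates at 31 to 69% (roughly 38/3.29 = 12 points SD), type I error is 4.3% against 4.9% and power 82.2% against 83.4%. At 21 to 79% (roughly 18 points), they are 3.7% against 5.1% and 82.5% against 85.9%. The direction and order of size agree. The gain is a little larger here because the spread in the tranexamic acid arm does not shrink by the factor 0.70.

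**The case against.** The prespecified analysis is valid and matches the method used for the sample size. In every scenario the chi-square test keeps more than 80% power, so what is forgone lies above the design target. The 2% non-compliance was not simulated, but the inflation covers it: 354 × 0.98² = 340. All of this stands.

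The loss is also conditional. If centers do not differ, the two tests are equivalent. No center-level rates are given, so no one can say from the article that the test will run below 5%.

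A reader might take the 9 to 67% range as the spread among these 13 centers; spread uniformly it would have an SD of 58/√12 = 17 points. The article does not support that reading. The range covers intraoperative transfusion only, while the primary outcome runs to 30 days, and it comes from published series, so differences between studies are mixed with differences between centers. It is illustrative only. A reader might also infer that the trial is underpowered or the RR biased. Neither follows: the error is toward caution, and blocking within center protects the comparison.

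Finally, stratifying has a practical cost. Five of the 13 sites were not yet active, and late or small sites may contribute few patients, so a pooling rule is needed.

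What remains is that the analysis ignores the one factor the randomization was stratified on, and that including it costs nothing measurable when centers are alike.

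**Conclusion.** The point holds as an efficiency recommendation. The primary analysis does not reflect the stratified design, and the imbalance clause does not repair that. If centers differ, the test is conservative and the RR interval somewhat too wide. Over assumed SDs of 0, 10, 15 and 20 points the loss is about 0, 0.5 to 1, 1.5 to 2 and 3 power points, with type I error down to about 3.3 to 3.7% at 20 points. The direction is certain once centers differ. The size depends on a spread that the documents do not give, and on an RR of 0.70 that is constant across centers. Discretionary transfusion without a trigger makes some spread plausible but does not measure it. The sample size stands, the planned 80% power is met, and there is neither bias nor inflation of type I error.

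**What to change.** Before unblinding, amend the analysis wording as follows:

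- **Primary test:** Cochran-Mantel-Haenszel test stratified by center.
- **Primary estimate:** center-stratified Mantel-Haenszel RR with 95% confidence interval.
- **Small centers:** a rule set in advance that pools very small centers into one stratum, for example all those below a fixed enrolment.
- **Sensitivity analysis:** the chi-square test and unadjusted RR as now written.

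The cost is wording only. Center is known for every patient through the randomization, the Mantel-Haenszel RR is already named in the plan, and the sample size need not change. Timing matters, because a switch made after unblinding could look driven by the data.
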